**Methods:**

This is a randomized, sham-controlled trial that will recruit 80 children aged 2 to 6 years with a confirmed ASD diagnosis. The randomization of the first 8 participants in this study used a 1:1:1 ratio. To more effectively test the core hypothesis (ie, the efficacy of the combined intervention), greater statistical power will be concentrated on the intervention group (rTMS+AIT), and the randomization ratio was ultimately adjusted to 2:1:1—specifically, (1) rTMS combined with AIT (n=40), (2) rTMS alone (n=20), or (3) sham rTMS (n=20). Primary outcome measures include the Autism Behavior Checklist and Childhood Autism Rating Scale. Secondary outcomes are the Strengths and Difficulties Questionnaire and Repetitive Behavior Scale–Revised. Assessments will be conducted at baseline, an interim time point, and immediately after the intervention. Data will be analyzed using SPSS (version 25.0; IBM Corp).

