## Methods

### Design and Setting

This is a randomized, parallel-group, sham-controlled trial conducted at the Shenzhen Longgang District Maternal and Child Health Hospital. The flowchart of the experimental design is shown in Figure 1, and the schedule of participant assessments is shown in Table 1. Specifically, participants are randomly assigned in a 2:1:1 ratio to 1 of 3 intervention groups: rTMS combined with AIT, rTMS alone, or sham stimulation. Sham stimulation is used via a “sham coil” with an identical appearance to that of the active TMS coil. Participants, outcome assessors, treating therapists, data analysts, and other study personnel are kept blind to group allocation throughout the trial.

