### Intervention Protocol

All participants receive conventional comprehensive rehabilitation treatment, including speech and cognitive training, social skill training, occupational therapy, sensory integration training, and music therapy [35,36], for 30 minutes per session once daily, 5 times per week, for 12 weeks in total.

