### Statistical Analysis

Statistical analyses will be conducted using SPSS. All participants, including the first 8 randomized under the original scheme, will be analyzed according to the intention-to-treat principle. At baseline, continuous variables among the 3 groups will be compared using the Kruskal-Wallis test, whereas categorical variables will be compared using the chi-square test to assess the balance of demographic and clinical characteristics (including age, gender, and baseline scores on all outcome measures) across the randomized groups.

Data normality will be assessed, and appropriate statistical tests will be selected accordingly. For normally distributed measurement data, between-group comparisons will be conducted using one-way ANOVA, and within-group pretest-posttest treatment comparisons will be made using paired-sample 2-tailed *t* tests presented as means and SDs. For nonnormally distributed data, nonparametric tests will be used, with results reported as medians and IQRs. *P*<.05 will be considered statistically significant.

In addition to the primary end-point comparisons at study completion, an exploratory interim analysis of outcomes at 6 weeks will be performed to preliminarily assess the effects of left DLPFC stimulation.

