### Protocol Amendment

This study randomized the first 8 participants in a 1:1:1 ratio. Subsequently, to more effectively test the core hypothesis (ie, the efficacy of the combined intervention), greater statistical power will be concentrated on the intervention group (rTMS+AIT), and the randomization ratio was ultimately adjusted to 2:1:1.

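### Within-arm before-after tests at P<.05 are not limited to description; with every child in rehabilitation and arms of 40/20/20, they reach significance more often in the combined arm at equal change

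*Protocol article*

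**What the plan says.** All references are to the protocol article.

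- **Analysis (Statistical Analysis).** For normally distributed data, "between-group comparisons will be conducted using one-way ANOVA", and in the same sentence "within-group pretest-posttest treatment comparisons will be made using paired-sample 2-tailed" t tests. Non-normal data get nonparametric tests. One threshold follows for everything: P"<.05 will be considered statistically significant". The section labels the 6-week analysis as exploratory but gives the paired tests no such label.
- **Background treatment (Intervention Protocol).** "All participants receive conventional comprehensive rehabilitation treatment", "for 30 minutes per session once daily, 5 times per week, for 12 weeks in total". The Exclusion Criteria rule out children who have already had ASD-specific intervention or comprehensive rehabilitation, so this treatment is new to all of them.
- **Allocation.** Under Design and Setting, "participants are randomly assigned in a 2:1:1 ratio to 1 of 3 intervention groups". The Abstract gives the sizes: "1) rTMS combined with AIT (n=40), (2) rTMS alone (n=20), or (3) sham rTMS (n=20". The Protocol Amendment section gives the reason: "greater statistical power will be concentrated on the intervention group (rTMS+AIT").

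**The concern.** A paired test within one arm asks whether that arm changed. It does not ask whether the arms changed differently, and it makes no use of the randomised comparison. In this trial some change is plausible in every arm, sham included. The children are 2 to 6 years old, they start daily rehabilitation at entry, and their parents complete the ABC, SDQ and RBS-R.

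The unequal allocation adds a second problem. For the same true mean change, an arm of 40 has a larger expected t statistic than an arm of 20. A results table with one P value per arm can therefore show significance in the combined arm and none in rTMS alone or sham when the three arms improved by exactly the same amount. The article already anticipates that the combination will do better than rTMS alone, and such a table would seem to confirm it.

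**Working it through.** **Inputs from the article.** Arms of 40, 20 and 20 (Abstract); two-sided paired t test at 0.05 (Statistical Analysis); about 20% dropout (Sample Size), which gives 0.8 × 40 = 32 and 0.8 × 20 = 16 completers.

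**Assumed.** The article gives no standardised change, meaning mean change divided by the SD of change (d). I take d equal in all arms and vary it from 0 to 1.0.

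**The plan's own figure.** The article states no power or error rate for the within-arm tests, so there is nothing to reproduce. Its 15 per group belongs to the between-group ANOVA and does not enter here.

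**Step 1: chance that one arm is significant.** With n children, the paired t statistic follows a noncentral t distribution with n − 1 degrees of freedom and noncentrality d√n. At d = 0.4 the noncentrality is 0.4 × √40 = 2.53 in the combined arm and 0.4 × √20 = 1.79 in a control arm. The chances of P<.05 are 0.694 and 0.397.

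**Step 2: chance of a discordant pair.** The arms are independent. Write A for the chance in the combined arm and B for the chance in a control arm.

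- Combined significant, rTMS alone not: A(1 − B) = 0.694 × 0.603 = 0.42.
- The reverse: B(1 − A) = 0.397 × 0.306 = 0.12.

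The same figures hold for sham in place of rTMS alone.

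**Results at 40 v 20:**

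| d, same in all arms | Combined arm significant | Control arm significant | Combined yes, rTMS alone no | Reverse |
|---|---|---|---|---|
| 0 | 5% | 5% | 5% | 5% |
| 0.2 | 23% | 14% | 20% | 10% |
| 0.3 | 46% | 25% | 34% | 13% |
| 0.4 | 69% | 40% | 42% | 12% |
| 0.5 | 87% | 56% | 38% | 7% |
| 0.6 | 96% | 72% | 27% | 3% |
| 0.8 | 99.9% | 92% | 8% | 0.1% |
| 1.0 | about 100% | 99% | 1% | about 0% |

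The peak is 42%, near d = 0.41. With completers only (32 v 16) and d = 0.5, the arms are significant in 78% and 46%, and the discordant patterns occur in 42% and 10%.

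**Step 3: both control arms non-significant.** The chance is A(1 − B)². At d = 0.4 and 40/20/20 it is 0.694 × 0.603² = 0.25. Over all values of d it peaks at about 27%, both at 40/20/20 and at 32/16/16.

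**Step 4: the share due to unequal allocation.** At 20 v 20 and d = 0.4, each discordant pattern has chance 0.397 × 0.603 = 24%. The 2:1 allocation turns 24% v 24% into 42% v 12%.

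**Step 5: on the ABC scale.** Take the Sample Size SD of 6.5 and assume a pre-post correlation r. The SD of change is 6.5 × √(2(1 − r)), which is 6.5 at r = 0.5. An equal 3-point fall in every arm is then significant in 81% (n = 40) v 50% (n = 20). At r = 0.3 this is 67% v 38%, and at r = 0.7 it is 96% v 72%.

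**Step 6: the between-arm test under the same conditions.** In 20,000 simulated trials at 40/20/20 with d = 0.5 in every arm, one-way ANOVA on change rejected in 5.1%, against a nominal 5%. The unequal allocation therefore does not distort the randomised comparison. The asymmetry belongs to the within-arm tests.

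**The case against.** The strongest reply is that the randomised comparison is already in the plan. The ANOVA is named before the paired tests, the sample size rests on it, and both the objective and the hypothesis in the Discussion are worded as comparisons between arms. This stands. A reader might infer that superiority will be declared because one arm is significant and another is not, but no section states such a rule. The risk is that results will be misread; no invalid primary analysis is planned.

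Three further inferences go beyond the documents:

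- *That the paired tests are planned as tests of treatment effect.* The article does attach the word treatment to these comparisons. In context it may mean no more than scores before and after treatment, in contrast to the between-group comparisons. The point does not need the stronger reading.
- *That significance in the combined arm alone is the likely result when the arms do not differ.* It never reaches half: the maximum is about 42% against one control arm and about 27% against both. If rehabilitation produces a large change in these previously untreated children, nearly every arm is significant and the asymmetry almost disappears.
- *That regression to the mean drives the change.* Entry rests on a DSM-5 diagnosis with no minimum ABC or CARS score, so the article gives no specific ground for this.

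It can also be said that a condensed article leaves the interpretation of secondary results to a fuller document. That would answer a complaint about missing detail. Here the article itself states the tests and a common threshold, and it marks a lesser role only for the 6-week analysis.

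**Conclusion.** The concern holds in limited form. The within-arm P values cannot show an effect of rTMS or AIT, because every arm receives the same new rehabilitation and the tests do not use the control arms. At equal change they reach significance more often in the combined arm than in a control arm. For a change of 0.2 to 0.6 SD at 40 v 20, the misleading pattern against rTMS alone occurs in 20% to 42% of trials, which is about 2 to 9 times as often as its reverse (20/10 at 0.2 SD, 27/3 at 0.6 SD). With no change the two patterns are equally frequent, and at 1.0 SD both are rare.

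The asymmetry lies in the chance of P<.05 and not in the estimated mean change, which is unbiased for the change in each arm. The sizes rest on an assumed standardised change that is the same in all arms. The direction rests only on the stated arm sizes and on a change that is neither zero nor very large.

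**What to change.** In Statistical Analysis, replace the paired tests (and their nonparametric counterparts) with a descriptive report of change in each arm: mean with 95% CI, or a median-based equivalent for non-normal data, without P values. Add one sentence saying that every efficacy claim, including combined v rTMS alone and combined v sham, rests on between-arm differences at T2.

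The cost is wording and fewer P values. No data collection, sample size or allocation changes. Table 2 places the analysis in March to June 2026, so the change should be made and dated before then.

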### Protocol Amendment

This study randomized the first 8 participants in a 1:1:1 ratio. Subsequently, to more effectively test the core hypothesis (ie, the efficacy of the combined intervention), greater statistical power will be concentrated on the intervention group (rTMS+AIT), and the randomization ratio was ultimately adjusted to 2:1:1.

## Results

### Overview

This study commenced data collection in April 2024. It is anticipated that the rTMS combined with AIT intervention will exhibit superior efficacy compared to rTMS only.

Currently, 8 participants (5 male and 3 female) have been recruited and randomized. Due to the limited sample size, this study has not yet conducted statistical comparisons of baseline characteristics among the 3 groups. The pooled baseline characteristics of the enrolled participants are as follows: mean age of 4.12 years, mean total ABC score of 53.38, and mean total Childhood Autism Rating Scale (CARS) score of 35.25. Recruitment and follow-up of all participants are ongoing.

### Study Timeline and Status

The detailed time points and status of this study are shown in Table 2.

**Table 2. T2:** Study timeline and status notes.

Period	Research activities	Status
January 2024-March 2024	Final protocol development and ethics approval	Completed
April 2024	Recruitment and randomization commenced	From the first participant onward, we consistently used a gender- and age-stratified randomization method.
May 2024-September 2025	Data collection and intervention; protocol refinement	Ongoing. All participants have received interventions per the established protocol. Interim assessments (6 weeks) and baseline evaluations as predefined assessment points have been conducted since study initiation. The first 8 participants were randomized at the initial 1:1:1 ratio. To enhance statistical power for effect size and variability in the combined intervention group (rTMS^a^+AIT^b^), the ratio was ultimately adjusted to 2:1:1.
October 2025-March 2026	Data collection and intervention; recruitment completion	Ongoing; strictly following protocol
March 2026-June 2026	End point assessment; data collation and analysis	Future work

a rTMS: repetitive transcranial magnetic stimulation.

b AIT: auditory integration training.

## Discussion

We hypothesize that, compared to the sham stimulation control group, participants with ASD receiving the active rTMS combined with AIT intervention will exhibit significant improvements in core symptoms such as social difficulties and stereotyped behaviors as measured using standardized scales such as the ABC, CARS, RBS-R, and SDQ. This study aims to provide the latest evidence-based support for the efficacy of this combined intervention approach.

Although preliminary studies have reported positive effects of rTMS combined with AIT in ASD, most have lacked blinding and placebo controls. By implementing a double-blind, sham-controlled design, this trial will address that key methodological limitation. If the results align with our hypotheses, they will provide the first clear demonstration of the specific therapeutic benefits of this combined intervention, thereby advancing the evidence level in this field from the exploratory stage to preliminary validation.

The core strength of this study lies in its rigorous methodological design. As a prospective randomized controlled trial, it uses a double-blind, sham stimulus–controlled approach, which minimizes the potential for expectation and observer biases during the evaluation process, thereby strengthening the causal inferences that can be drawn from the observed efficacy differences. Additionally, the study uses recognized, standardized assessment tools, including the ABC, CARS, SDQ, and RBS-R, to provide a comprehensive and objective evaluation of the core symptom domains in ASD. This assessment combination ensures good reliability and clinical relevance of the study results. Finally, the rTMS and AIT interventions are noninvasive, well tolerated, and easy to implement in clinical settings. These features support participant compliance and trial feasibility and, if the interventions prove effective, will facilitate wider clinical translation as a safe, scalable treatment option for children with ASD.

This study also has some important limitations. First, while rigorous behavioral assessments are used, neurophysiological indicators (eg, EEG and functional near-infrared spectroscopy) are not included. Therefore, this study cannot directly reveal the underlying neural mechanisms of the combined intervention. Future studies should verify these mechanisms in conjunction with neuroimaging techniques. Second, the primary objective is to preliminarily evaluate whether adding AIT to rTMS could yield superior clinical efficacy. As a result, a separate control group receiving AIT alone was not established. Subsequent studies will need to expand the sample size to explore this question. Additionally, the follow-up period after the intervention may be insufficient to assess the long-term durability of the effects, so our conclusions will be limited to discussing the short-term efficacy.

On the basis of the expected results and limitations of this study, future research should focus on the following directions. First, at the mechanistic level, follow-up studies should integrate neuroimaging techniques such as EEG, functional near-infrared spectroscopy, or functional magnetic resonance imaging to directly observe the effects of the combined intervention on brain network connectivity and neural activity. Second, at the level of efficacy optimization, trials with larger sample sizes, longer follow-up periods (eg, 6 months or 1 year), and inclusion of an AIT-only group will be needed to verify the durability of the intervention’s benefits and clarify the individual vs additive benefits of rTMS and AIT.

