**Objective:**

This study aims to evaluate the clinical efficacy of a combined rTMS and AIT intervention compared to rTMS alone and sham stimulation in children with ASD.

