**Conclusions:**

This will be the first sham-controlled trial to systematically investigate the potential synergistic effects of a combined rTMS and AIT intervention in children with ASD. The results will provide valuable insights into the neurotherapeutic potential of this combined approach and contribute to the development of evidence-based interventions for ASD.

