Although preliminary findings from these individual interventions are encouraging, the evidence base for their combined application remains limited and is subject to methodological constraints. To our knowledge, the few existing studies on combined rTMS and AIT lack adequate control conditions and are susceptible to placebo effects and observer bias [27,28]. A critical and pervasive limitation in recent studies of noninvasive brain stimulation interventions for ASD is the absence of high-quality sham-controlled trials [29,30]. This significant methodological gap prevents definitive conclusions about the true synergistic efficacy of these combined interventions. Consequently, there is an urgent need for rigorous, well-controlled research evaluating the synergistic effects of these 2 treatment modalities to provide stronger evidence-based support for ASD interventions.

The primary objective of this study is to investigate whether the combination of rTMS and AIT produces superior effects on brain activity and behavior outcomes in children with ASD compared to sham-controlled conditions. We hypothesize that the combined intervention will yield synergistic benefits, and the findings from this study are expected to provide a scientific foundation for optimizing clinical interventions for ASD.

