### Sample Size

Sample size calculation was based on one-way ANOVA comparing the primary outcome measure (Autism Behavior Checklist [ABC] scores) among the 3 groups. The calculation was performed using the PASS software (version 15; NCSS, LLC) with the following parameters: significance level of α=.05 (2 sided), statistical power of 1 – β = 0.90, and number of groups of *k*=3. On the basis of previous similar studies [33,34], the within-group SD is set at σ=6.5, yielding a medium to large effect size (Cohen *f*). The calculation indicated that a minimum sample size of 15 participants per group was required. Accounting for an anticipated dropout rate of approximately 20%, a total of 20 participants will be recruited for each group. The following standard ANOVA sample size formula was applied: n = ψ^2^ × (σ^2^) / (*k* × *d*^2^).

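### The primary question has two different comparators and one or two primary scales, and the only between-group test named, a three-group ANOVA, cannot show that adding AIT helps

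*Protocol article*

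**What the plan says.** **Objective.** The Abstract's Objective names both comparators: the study is to "evaluate the clinical efficacy of a combined rTMS and AIT intervention compared to rTMS alone and sham stimulation in children with ASD". The Introduction's primary objective is whether the combination "produces superior effects on brain activity and behavior outcomes in children with ASD compared to sham-controlled conditions". The limitations paragraph of the Discussion gives another: "the primary objective is to preliminarily evaluate whether adding AIT to rTMS could yield superior clinical efficacy". The hypothesis that opens the Discussion is against sham, while the result anticipated in the Results is superiority over rTMS only.

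**Synergy.** The Abstract's Conclusions say the trial will "systematically investigate the potential synergistic effects of a combined rTMS and AIT intervention", and the Introduction hypothesises synergistic benefit. The limitations concede that there is no AIT-only group and that neurophysiological measures are not included. Table 1 schedules four behavioural scales and nothing else.

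**Primary scale.** In the Abstract, "Primary outcome measures include the Autism Behavior Checklist and Childhood Autism Rating Scale", and Outcome Measures lists both under the primary heading. Sample Size rests on a "one-way ANOVA comparing the primary outcome measure (Autism Behavior Checklist [ABC] scores) among the 3 groups".

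**Test.** Statistical Analysis names one-way ANOVA for between-group comparisons of normally distributed data and nonparametric tests otherwise. One threshold applies throughout: P<.05 "will be considered statistically significant".

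**The concern.** The comparator decides what the trial can claim. Combined versus sham mixes the effects of rTMS and AIT. Combined versus rTMS alone isolates AIT given with rTMS. Synergy is an interaction, and estimating it needs an AIT-only arm. The article gives the label of primary objective to the first in one place and to the second in another, and sets the third as its hypothesis.

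The test that is named and sized answers none of them. A three-group F test asks whether any of the three means differ, so rTMS beating sham is enough to make it significant. The Discussion nevertheless says that results in line with the hypotheses would be a first clear demonstration of benefits specific to the combination.

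Two primary scales with no rule for combining them also leave the overall error rate undefined.

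**Working it through.** **1. The plan's own figure.** Inputs from Sample Size: k=3, α=.05, power 0.90, SD 6.5, 15 evaluable per group, dropout about 20%, 20 recruited per group. No target difference or numerical Cohen f is given, so the 15 cannot be reproduced. Solving backwards with the noncentral F distribution (λ = N·f², N=45, df 2 and 42), 15 per group reaches 90% power at f=0.55. The dropout step is consistent: 15/0.8 = 18.75, so 19, against 20 stated. The 90% therefore belongs to the omnibus test at f=0.55.

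**2. The omnibus test when AIT adds nothing.** Assume combined and rTMS alone are both d SD better than sham (d is an assumption). Then λ = Σ nᵢ(μᵢ − μ̄)², in SD units.
- 40/20/20, d=0.8: μ̄ = 60×0.8/80 = 0.6; λ = 60×0.2² + 20×0.6² = 9.6; critical F(2,77) = 3.12; probability of significance 0.78.
- 32/16/16 (20% dropout), d=0.8: λ = 48×0.2² + 16×0.6² = 7.68; critical F(2,61) = 3.15; probability 0.68.

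| Gain of both active arms over sham | 40/20/20 | 32/16/16 |
|---|---|---|
| 0.5 SD | 38% | 31% |
| 0.8 SD | 78% | 68% |
| 1.0 SD | 94% | 87% |

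The true AIT effect is zero in every cell. The 40/20/20 split is nominal, since the first 8 children were randomised 1:1:1.

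**3. Two primary scales at .05 each.** If success on either counts and the scales are independent, the error is 1 − 0.95² = 9.75%. Simulating two omnibus tests under no effect at 32/16/16 gives about 10%, 9% and 8% at between-scale correlations of 0, 0.5 and 0.8. If both must be significant, the error is at most 5%.

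**4. Power of the contrast that isolates AIT.** Two-sample t test, two-sided .05, noncentrality d/√(1/n₁ + 1/n₂). For 40 versus 20 at d=0.8: 0.8/√(1/40 + 1/20) = 2.92, giving 82%.

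| Assumed d, combined vs rTMS alone | 40 vs 20 | 32 vs 16 |
|---|---|---|
| 0.5 | 43% | 36% |
| 0.67 | 68% | 58% |
| 0.8 | 82% | 73% |

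The d=0.67 row links back to step 1. With f=0.55 and evenly spaced means, best and worst groups differ by 0.55×√6 = 1.35 SD, and neighbouring groups by half of that, about 0.67 SD or 4.4 points at SD 6.5.

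**The case against.** **The comparators overlap.** The Abstract's Objective names both, so the other two statements can be read as parts of it. That softens the conflict without removing it: an objective with two comparators still needs one that decides, and two passages name different ones as primary.

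**The limitations already concede the missing AIT-only arm and the missing brain measures.** They do, and the synergy wording in the Abstract's Conclusions is a closing remark. But brain activity stands in the primary objective, and synergy in the Introduction's hypothesis.

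**Contrasts and multiplicity rules belong in the analysis plan, which is not shown.** This stands. Their absence is no finding, and one cannot infer that comparator or scale will be chosen after the results are seen. The point rests on what is stated: conflicting objectives, conflicting counts of primary scales, and an omnibus test as the one sized.

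**Stronger numerical readings.** A reader might take the 68-78% as a false-positive rate. It is not: sham is truly worse in that scenario, so the rejection is correct. It simply says nothing about AIT. A reader might also count four to six unadjusted pairwise tests over the two scales and arrive at an error of 17% or 21% (correlation 0.5). The article states no such ungated tests. If pairwise tests follow only after a significant F, the error over both scales stays at about 8-10%, and then only if either scale counts.

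**Conclusion.** The concern holds in this form. The article contradicts itself on the comparator of the primary objective and on whether there are one or two primary scales. It includes an outcome that is not measured and an interaction that the design cannot estimate. The one between-group test it names and sizes cannot by itself show a benefit of adding AIT: with no AIT effect it is significant in 78% (40/20/20) or 68% (32/16/16) of trials if both active arms gain 0.8 SD over sham, and in 38-94% or 31-87% for gains of 0.5 to 1.0 SD. These gains are assumptions, as the article gives no target difference. Family-wise error is about 8-10% if either scale suffices and at most 5% if both are needed; the article leaves this open. A full analysis plan could add contrasts, but it could not reconcile two conflicting primary objectives in the protocol.

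**What to change.** By dated amendment before the end-point analysis, which the timeline places in March to June 2026:

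1. Name ABC at the posttreatment assessment (week 13) as the single primary scale, since the trial was sized on it.
2. Name combined versus rTMS alone as the deciding contrast, with one degree of freedom. It is the only one that isolates AIT, and it matches the limitations paragraph and the anticipated result.
3. Then test in fixed sequence, each at two-sided .05: combined versus sham on ABC, combined versus rTMS alone on CARS, combined versus sham on CARS. Treat rTMS versus sham as supportive.
4. Remove brain activity from the objective, and replace synergy with the added benefit of AIT given with rTMS.
5. State the power of the deciding contrast for a named target difference.

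This needs no new participants, visits or measurements, but it is more than a wording change. Once a test in the sequence fails, later ones are not confirmatory, so a failed first contrast would also remove confirmatory status from combined versus sham, the hypothesis in the Discussion. The first contrast has only about 36% to 73% power with 32 versus 16 at d=0.5 to 0.8. If the investigators prefer a different order, they should fix and justify it in the same amendment.
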